### Statistical analysis

For both groups, the distribution of continuous data will be presented using mean, standard deviation (SD), minimum, maximum, and median, and for categorical variables, absolute and relative frequencies will be used. The primary endpoint, which is the modified BOSATS score, will be compared between both groups using a *t* test with a significance level of 0.05. Comparisons regarding secondary endpoints will be performed by the chi-square test for categorical data and the *t* test for continuous variables. Resulting *p* values from secondary analyses will be interpreted descriptively.

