### Basic skills training

All trainees will attend the MIS training center of the Department of General, Visceral, and Transplantation Surgery at Heidelberg University Hospital and perform 10 hours of standardized basic skills training. This includes instrument coordination tasks as well as laparoscopic suturing and knot tying exercises with box trainers. At the end the trainees will perform basic skills tasks with the VR trainer for one hour as a pre-test (Table 1).

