### Pre-test

The pre-test for both groups includes the laparoscopic basic skills training tasks in the VR trainer. Groups A and B will perform eight basic skills tasks before starting with E-learning. The objective for these exercises is to learn about the VR trainer management and functions to train for their RYGB performances (Table 1).

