### Randomization

Trainees are randomly allocated to either the checklist group (group A) or control group (group B) with the sealed envelopes technique. The randomization of subjects is performed in a 1:1 ratio by block randomization with a variable block length using a computer-generated randomization list. Trainees are allocated to groups without stratification by gender or previous operative experience. The employee responsible for the randomization and group assignment is otherwise not involved with the training, tests, and data from the present study. As student recruitment to the study will be completed before randomization, any influence of randomization results or subsequent task assignments is considered minimal. We aim to compare both groups following data acquisition.

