### Secondary endpoints

The secondary endpoints include the time spent on the VR trainer to perform RYGB; time will be taken at all three times the students perform the procedure. VR trainer subscores and single parameters for each trainee will be evaluated. Also, trainees’ laparoscopic small bowel suturing performance will be included and evaluated with an OSATS scale. Additional endpoints include subgroup analyses of gender differences, gaming experience, and questionnaire evaluations of training after the course. Previous studies state that since surgery has been traditionally a male field, male students acquire surgical skills faster and have superior visuospatial skills than female students [21–24].

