### Sample size determination

Sample size determination was calculated for the BOSATS score. Previous published data from a study by Zevin et al. was used. The data was modified according to the BOSATS with a maximum score of 115 points. Group 1 had a mean score of 95.8 points with an SD of 9.9, while group 2 had a mean of 82.9 points with an SD of 15.0. Calculation was done for a significance level of *α* = 0.05 and a power of 1 − *β* = 0.8. An additional 10% was added to each group to compensate for the adjustment of the data. With these data differences can be detected with a minimum of 24 trainees in each group. To account for possible drop-outs the planned group size is 40 trainees per group.

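### The primary t test is valid but unadjusted, although all trainees take a VR pre-test before the arms diverge; adjusting for it and for gender would be a cheap gain in precision of unknown size

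*Protocol article*

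**What the plan says.** All references are to the protocol article.

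- **Statistical analysis.** "The primary endpoint, which is the modified BOSATS score, will be compared between both groups" by a t test, described as a "test with a significance level of 0.05". No covariate is named.
- **Basic skills training.** "At the end the trainees will perform basic skills tasks with the VR trainer for one hour as a pre-test".
- **Pre-test.** "Groups A and B will perform eight basic skills tasks before starting with E-learning". The section gives the purpose as becoming familiar with the VR trainer ahead of the bypass procedure, and defines no summary score.
- **Order of events.** The abstract places the basic VR training before randomization. The section on the introduction to RYGB by E-learning places E-learning after it.
- **Randomization.** "Trainees are allocated to groups without stratification by gender or previous operative experience".
- **Secondary endpoints.** Citing earlier studies, the section says that "male students acquire surgical skills faster and have superior visuospatial skills than female students". It plans subgroup analyses by gender and by gaming experience.
- **Primary endpoint.** This is a blinded expert's modified BOSATS rating of a four-step RYGB on the VR trainer.

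**The concern.** A measurement that precedes the intervention cannot be affected by it, so it is a legitimate covariate. The pre-test meets that condition, and it is taken on the machine used for the primary endpoint. If it predicts the BOSATS score, a t test that ignores it leaves explainable variation in the error term. The interval is then wider than it need be, and any chance difference in skill between the arms stays in the point estimate.

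The same reasoning covers gender. The article treats it as related to how fast skills are acquired, and must record it for the planned subgroup analyses. It enters neither the allocation nor the primary comparison. What is at stake is the width of the interval and the ability to detect effects smaller than the one planned for.

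**Working it through.** **Inputs (Sample size determination section).** "Group 1 had a mean score of 95.8 points with an SD of 9.9"; group 2 had mean 82.9 and SD 15.0. The difference is 95.8 − 82.9 = 12.9. Power is 0.80 and alpha 0.05, taken as two-sided because the article does not say. The stated minimum is 24 per group and the planned size 40 per group.

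**The plan's own figure.** With the larger SD and the normal approximation, n = 2 × (1.96 + 0.84)² × 15.0² / 12.9² = 21.22 per group. Adding 10% gives 23.35, hence 24. The stated figure reproduces on this route, although the article does not say that the larger SD was used.

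**Unadjusted precision at 40 per group.** Root-mean-square SD = √((9.9² + 15.0²)/2) = 12.71. Standard error of the difference = 12.71 × √(2/40) = 2.84. With 78 degrees of freedom the 95% half-width is 1.99 × 2.84 = 5.66 points. The difference detectable with 80% power (noncentral t) is 8.06 points.

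**Adjusted precision.** ANCOVA on a covariate with correlation ρ to the outcome has residual SD 12.71 × √(1 − ρ²). The article gives no value for ρ, so a range is assumed:

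| Assumed ρ | 1 − ρ² | 95% half-width (points) | Narrowing | Detectable difference (points) |
|---|---|---|---|---|
| none (t test) | 1.00 | 5.66 | – | 8.06 |
| 0.2 | 0.96 | 5.54 | 2% | 7.90 |
| 0.3 | 0.91 | 5.40 | 5% | 7.69 |
| 0.5 | 0.75 | 4.90 | 13% | 6.98 |
| 0.6 | 0.64 | 4.53 | 20% | 6.45 |

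The table allows for one covariate. A second one takes one more degree of freedom (76 instead of 77) and changes no entry by more than about 0.01 points. Anything that gender explains beyond the pre-test is not counted.

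**Power.** For the planned 12.9 points, the unadjusted t test at 40 per group has power 0.994 with SD 12.71 and 0.967 with SD 15.0. For half that difference, 6.45 points, with SD 12.71, power is 0.61 unadjusted and 0.65, 0.74 or 0.80 with adjustment at ρ = 0.3, 0.5 or 0.6.

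**Type I error.** In 100,000 simulated trials of 40 per group at each of ρ = 0, 0.3, 0.5 and 0.7, the unadjusted t test rejected a true null hypothesis in 4.9% to 5.0% of runs.

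**Chance imbalance.** The standard error of a standardised baseline difference is √(2/40) = 0.224. An imbalance above 0.3 SD in either direction therefore has probability 2 × (1 − Φ(0.3/0.224)) = 0.18. An imbalance of exactly 0.3 SD shifts the unadjusted difference by 0.3 × ρ × 12.71, which is 1.1, 1.9 or 2.3 points at ρ = 0.3, 0.5 or 0.6. The half-width of 5.66 points already allows for such shifts.

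**The case against.** The strongest reply is that nothing here is an error. An unadjusted t test in a 1:1 randomised trial is valid, chance imbalance is not bias, and power for the planned difference is ample. All of this stands. A reader might infer from the missing adjustment that the primary result is biased or the trial underpowered; the simulation and the power figures above rule out both readings.

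The second reply is that the pre-test is not a baseline of the endpoint. It consists of generic tasks such as camera handling, clipping and peg transfer. The BOSATS items also cover procedural steps such as locating the ligament of Treitz or confirming complete transection. All trainees first have 10 hours of standardised training, and the limitations section stresses how homogeneous they are in surgical experience. Either could weaken the correlation. This stands too. It is tempting to say that simulator aptitude is a main source of variation in the BOSATS score, but no section says so. A covariate need only precede the intervention and be predictive, so the objection limits the certainty and size of the gain without removing it.

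Third, gender is not ignored, since subgroup analyses by gender are planned. That is correct, but a subgroup analysis does not adjust the primary comparison.

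Fourth, adjusted analyses may sit in a fuller plan that is not shown. As supporting analyses they may. The article nevertheless fixes the primary test as the t test, and the point is confined to that choice.

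Finally, the Trial status section says that data collection has ended and analyses are running. Changing the primary test at this stage is therefore more than a change of wording; the fix takes this into account.

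**Conclusion.** The point holds as a recommendation on efficiency. The primary comparison is valid, but it does not use a pre-intervention measurement taken on every trainee, nor a factor that the article itself regards as related to skill acquisition.

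The benefit is small if the pre-test correlates with the BOSATS score at 0.2 to 0.3 and material at 0.5 or more. It matters mainly for interval width and for true effects well below 12.9 points. Such effects cannot be excluded: the planning difference is a standardised effect of 12.9/12.71 = 1.02, taken from another study's rescaled data.

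The figures rest on the assumed correlations, a linear relation, an SD of 12.71 unless another is stated, two-sided testing and 40 analysed trainees per group. The conclusion also assumes that pre-test results were stored. The Discussion mentions continuous recording by the VR trainer and of the tests, but names no pre-test score.

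**What to change.** First confirm that the pre-test results were recorded for each trainee. Then:

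- **If no group results have been seen:** define one pre-test summary score in writing, for example the mean z-score over the eight tasks. Make the primary analysis a linear model (ANCOVA) of the modified BOSATS score on group, that score and gender. Report the unadjusted t test as a sensitivity analysis.
- **If group results have already been seen:** keep the t test as primary and report the same ANCOVA as a clearly labelled supporting analysis. Give the date on which its covariates were fixed.

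The cost is two degrees of freedom out of 78, a dated amendment to the analysis text with its reason, and the check on the stored scores. No further trainees or measurements are needed.

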### Sample size determination

Sample size determination was calculated for the BOSATS score. Previous published data from a study by Zevin et al. was used. The data was modified according to the BOSATS with a maximum score of 115 points. Group 1 had a mean score of 95.8 points with an SD of 9.9, while group 2 had a mean of 82.9 points with an SD of 15.0. Calculation was done for a significance level of *α* = 0.05 and a power of 1 − *β* = 0.8. An additional 10% was added to each group to compensate for the adjustment of the data. With these data differences can be detected with a minimum of 24 trainees in each group. To account for possible drop-outs the planned group size is 40 trainees per group.

## Discussion

This study evaluates if students who rate videos with a checklist during E-learning will have a better learning curve while performing an RYGB in the VR trainer than those who do E-learning without the ratings and checklist. Rating videos seems like an extra training for students; therefore, expectations are that trainees who perform the video ratings will have a better performance than those who just use E-learning and no rating. The continuous data recording of the VR trainer and the tests will help us understand if there is a difference in learning curves between both training groups [25]. The assessments of the study trainees will help us to understand the possible factors of influence for successful surgical education. It is important to ascertain which module will have a better outcome to be implemented into further laparoscopic and bariatric surgery training.

### Limitations of the study

There are some limitations to the study; subjects are limited to be medical students in their clinical years. Participants’ lack of surgical knowledge and bariatric surgery experience may influence their performance during the study. On the other hand, the inclusion of laparoscopy-naïve medical students allows for better differentiation of intervention effects, as the study group is very homogenous concerning surgical experience. In addition, the students have a total of 11 hours of laparoscopy training using the box trainer and the VR trainer before performing the virtual RYGB after extensive E-Learning for this procedure. Due to the fact that the trainees are laparoscopic novice medical students, the results cannot be transferred directly to more experienced surgeons. However, the results will provide a better perspective for designing optimal bariatric surgery training.

## Trial status

Recruitment started in April 2016 and the collection of data was finished in August 2016. Data analyses are currently running.

## Abbreviations

BOSATS: Bariatric Objective Structured Assessment of Technical Skill
MC: Multiple choice test
MIS: Minimally invasive surgery
OSATS: Objective Structured Assessment of Technical Skill
RYGB: Laparoscopic Roux-en-Y gastric bypass
SD: Standard deviation
VR: Virtual reality
